### Inclusion and Exclusion Criteria

In WP1, WP2, and WP3, the inclusion criteria are youth aged 16 to 25 years who identify as belonging to at least one of the following groups: national minorities (Forest Finns, Jews, Kven or Norwegian Finns, Roma, and Romani), Indigenous Sámi youth, and refugees. The term “refugees” is used inclusively to refer to all youth who consider themselves to be refugees, regardless of their official status as defined by the national government. Moreover, the first 2 cohort surveys in WP1 also include youth aged 16 to 25 years who do not define themselves as belonging to any of these minority groups. WP3 also includes professionals working in health services, social services, and related sectors (eg, education) who engage directly with youth from minority backgrounds, as well as youth representatives aged 16 to 35 years who belong to any of the mentioned minority groups. Additional inclusion criteria for youth participating in the RCT in WP4 include a Patient Health Questionnaire (PHQ-9) score indicating mild to moderately severe depressive symptoms (scores from 5 to 19). Youth included in the qualitative study in WP4 are those who have been exposed to the adapted digital services. Youth aged <16 or >25 years are excluded from participation. Participants across all groups must provide written informed consent to take part in the research.

### Study Outcomes

Given the nature of the *InvolveMENT* project, specific primary and secondary outcomes are defined for the RCT (WP4), which is the only component designed to evaluate the effectiveness of adapted digital mental health services quantitatively.WP2 and WP3 are exploratory and developmental in nature and therefore do not include predefined outcome measures. The primary outcome is the PHQ-9 score at 12 months of the trial. The secondary outcomes include scores for Generalized Anxiety Disorder [29,30], the Flourishing Scale [31], and the Children’s Somatic Symptoms Inventory 8 [32]. These outcomes are based on self-report and may be influenced by factors such as cultural, language, and social differences in diverse minority populations. While no single outcome measure has been validated, and culturally adapted tools are lacking across the included minority ethnic groups, these commonly used instruments have been selected as a choice to support knowledge generation in the absence of more inclusive and adapted alternatives. Service acceptability will be assessed by calculating the proportion of participants who use the adapted services.

### Study Procedures

#### Participant Recruitment

Participant recruitment in WP1, WP2, and WP3 is conducted through a broad range of channels tailored to reach minority ethnic youth from diverse backgrounds. These include secondary schools nationwide—particularly those with introduction classes for refugee youth and those with higher proportions of Indigenous and national minority youth—as well as higher education institutions (including one for students with Indigenous backgrounds), health care services, and language learning centers. Recruitment also involves collaborating with the national minority youth organizations, which are partners in the project, using their networks and social media platforms. In addition, outreach is conducted via social media channels commonly used by these groups of youth populations, such as TikTok (ByteDance), Instagram (Meta Platforms), and Snapchat (Snap Inc.). Recruitment takes place nationwide to ensure a diverse representation of perspectives. Participants who wish to contribute further may contact the research team to express interest in taking part in qualitative interviews and co-design workshops. A rolling recruitment method will be used over a period of 1 year for WP1 and WP4.

In the evaluation phase (WP4), participants for the RCT are selected from among those who scored between 5 and 19 on the PHQ-9 at baseline, indicating mild to moderately severe symptoms of depression. Participants for qualitative interviews in this phase are recruited based on their experience with the adapted digital mental health services.

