### Study Population

Throughout all phases of the project, participants will be recruited among youth who identify as belonging to at least one of the following groups: national minorities (Forest Finns, Jews, Kven or Norwegian Finns, Roma, and Romani), Indigenous Sámi youth, and refugees. In addition, in the first 2 of 3 cohort surveys (WP1), youth not belonging to the mentioned minority groups will be included. The inclusion of the broader group of youth will enable comparisons between minority and nonminority youth. During the co-design phase (WP3), professionals working in health and social services who engage directly with these youth groups will also be recruited.

In WP1, up to 1500 youth with minority backgrounds will be recruited for each of the 3 cohort surveys. Additionally, the first 2 cohort surveys will include up to 1500 youth who do not identify as belonging to the described minority groups. WP2 will include 50 to 100 youth from the different minority groups, ensuring representation across all groups. WP3 will involve a minimum of 50 youth and professionals. WP4 will recruit approximately 300 youth from the WP1 cohort for an RCT and 25 to 45 youth for a qualitative study based on their exposure to the adapted digital services, regardless of RCT participation.

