#### Randomization

In WP4, participants who meet the inclusion criteria will be randomly allocated in a 1:1 ratio using Microsoft Excel, either to receive the intervention (the adapted digital services) or to continue with usual care as part of the control group. Those assigned to the control group will not be informed that they are part of a trial or that other participants are receiving an intervention. This approach is consistent with the TwiCs design [27,33], which stages and tailors the consent process to reflect real-world clinical practice. The design ensures that individuals receiving usual care are not informed about treatments they will not be offered, thereby minimizing potential for disappointment bias.

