### Statistical Considerations and Data Analysis

#### Sample Size Calculation

Approximately 25% of youth are expected to experience mild to moderately severe symptoms of depression (PHQ-9 scores of 5‐19) [9,12,47]. To ensure a sufficient number of eligible participants for the RCT (WP4), a population cohort of 1500 youth will be recruited. This cohort size is designed to provide an adequate number of individuals who meet the inclusion criteria, which are scores of mild to moderately severe range on the PHQ-9, and to account for potential exclusions due to eligibility, nonconsent, or attrition. On the basis of an anticipated 20% dropout rate, 80% statistical power, a significance level of 0.05, and a moderate effect size of 0.35 (Cohen *d*), with equal allocation between intervention and control groups, the required sample size for the RCT is estimated to be 294. This has been rounded up to 300 to maintain sufficient power and accommodate potential variability.

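### The plan does not settle whether all eligible cohort members or only about 300 are randomised, and stopping at 300 gives about 77% power, not the stated 80%

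*Protocol article*

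**What the plan says.** Four sections of the protocol article bear on who enters the RCT.

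- Participant Recruitment: "participants for the RCT are selected from among those who scored between 5 and 19 on the PHQ-9 at baseline". It does not say how the selection is made.
- Randomization: "participants who meet the inclusion criteria will be randomly allocated in a 1:1 ratio". It names no limit and no sampling step.
- Study Population: "WP4 will recruit approximately 300 youth from the WP1 cohort for an RCT".
- Sample Size Calculation: a required total of 294, rounded up to 300. The inputs are "80% statistical power", "a significance level of 0.05", "a moderate effect size of 0.35" (Cohen d), equal allocation and 20% dropout.

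The last section also states the size of the eligible pool: "Approximately 25% of youth are expected to experience mild to moderately severe symptoms of depression (PHQ-9 scores of 5‐19", in a cohort of 1500. It explains that the cohort is made this large so that enough eligible youth remain after exclusions, nonconsent and attrition.

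The section on data collection and follow-up places the RCT baseline at the 6-month cohort survey and its follow-up at the 18-month cohort survey. Study Population plans for up to 1500 minority youth at each of the three surveys.

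**The concern.** The randomised population is a basic element of the design, and a reader cannot tell from these sections what happens to an eligible youth once about 300 have been randomised. That would be a small matter of wording if 300 were comfortably enough. It is not enough on the plan's own inputs, while the plan expects more than 300 eligible youth.

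In a Trials within Cohorts design, anyone eligible but not randomised stays in the cohort and is due to complete the PHQ-9 at 18 months regardless. If the trial stops at 300, it falls short of its stated power while leaving unused primary-outcome data that the project plans to collect anyway.

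**Working it through.** **Inputs.** All come from Sample Size Calculation: d = 0.35, alpha = 0.05, power 80%, 1:1 allocation, 20% dropout, 25% eligible, cohort 1500. The article does not say whether alpha is one- or two-sided; two-sided is assumed, and one-sided was also tried.

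**Step 1: the plan's own figure of 294.** For a two-sample comparison of means, evaluable n per arm = 2 × (1.960 + 0.842)² / 0.35² = 128.1, rounded up to 129, or 258 in total. The t-test version gives 130 per arm, 260 in total.

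| Version | Evaluable total | Divided by 0.80 | Multiplied by 1.20 |
|---|---|---|---|
| Two-sided, normal | 258 | 323 | 310 |
| Two-sided, t-test | 260 | 325 | 312 |
| One-sided, normal | 202 | 253 | 243 |

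None of these gives 294. Dividing by 0.80 is the right adjustment for 20% dropout, so the stated inputs require about 323 to 325 randomised.

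**Step 2: power if 300 are randomised.** Evaluable: 300 × 0.80 = 240, or 120 per arm. Power = Φ(0.35 × √(120/2) − 1.960) = Φ(0.751) = 77.4%; the t-test gives 77.0%. At 294 it is 76.5% (t-test 76.2%).

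**Step 3: the expected pool.** 0.25 × 1500 = 375, and 375 − 300 = 75. This is before any loss between cohort entry and randomisation.

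**Step 4: how much of the pool survives to randomisation.** The documents give no percentage for this loss, so a range is assumed. Power is for all remaining eligible youth randomised 1:1, followed by 20% dropout.

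| Loss before randomisation (assumed) | Randomised | Above 300 | Evaluable per arm | Power (normal) | Power (t-test) |
|---|---|---|---|---|---|
| 0% | 375 | 75 | 150 | 85.8% | 85.6% |
| 10% | 338 | 38 | 135 | 82.0% | 81.7% |
| 20% | 300 | 0 | 120 | 77.4% | 77.0% |
| 30% | 263 | −37 | 105 | 71.8% | 71.4% |

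At 325 randomised (130 evaluable per arm), power is 80.6% (t-test 80.3%). That number is available as long as no more than 1 − 325/375 = 13% of the pool is lost before randomisation.

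**Step 5: detectable effect at 80% power.** This is (1.960 + 0.842) × √(2/n): 0.362 with 120 per arm and 0.323 with 150 per arm.

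**The case against.** The strongest reply is that the sections are compatible. There is one eligibility rule, a PHQ-9 score of 5 to 19. Selecting from among those youth may only name the source pool, and about 300 may be the number expected once losses are taken off. This largely stands. A reader might infer two conflicting definitions of the trial population, but the documents do not support that: the Randomization section does not say all, and no section states a cap. The text is ambiguous, not contradictory.

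A reader might also infer that the 300 would be hand-picked. Nothing in the article describes this, and the way trial members are drawn may be set out in a full protocol that is not shown.

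Nor can the surplus be treated as assured. Sample Size Calculation gives it a purpose, as a reserve against exclusions, nonconsent and attrition. Study Population describes the cohort as up to 1500, and Strengths and Limitations names recruitment as the main risk. So 75 is a maximum, and it vanishes at 20% loss before randomisation. On the other side, the 20% dropout is already meant to be inside the 294, and Study Design uses rolling recruitment to offset attrition, so some of the reserve may be counted twice.

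It is tempting to claim that the extra power is free, or to keep 150 youth in the offered arm and treat everyone else eligible as controls. Neither goes through as it stands. Randomising more youth 1:1 means more offers of the intervention. An unequal split would depart from the stated 1:1 ratio and is hard to fix in advance under rolling recruitment, when the final eligible count is unknown.

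Finally, the shortfall in power comes from the 294 itself, which is a separate arithmetic error. That is true, and correcting the target to about 325 would restore 80%. But the corrected target still has to be met from this pool, so whether all eligible youth are randomised still needs stating.

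**Conclusion.** The point holds as an ambiguity with a measurable consequence. The article does not say whether enrolment in the RCT ends at about 300 or takes in every eligible cohort member. If it ends at 300, power is about 77%, roughly 3 points below the stated 80%. If everyone eligible is randomised, power lies between about 77% (20% lost beforehand, no gain) and about 86% (no loss), a gain of at most about 8 points.

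These figures assume a two-sided test, d = 0.35, 20% dropout after randomisation, a cohort that reaches 1500 and 25% eligibility. If losses before randomisation exceed 20%, the trial falls below 300 under either reading and this change cannot rescue it. The change is worth making because it costs little and, with no more than about 13% lost beforehand, brings the trial to its own stated power.

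**What to change.** In Study Population, Participant Recruitment, Randomization and Sample Size Calculation, use one rule: every minority cohort member with a PHQ-9 score of 5 to 19 at the RCT baseline (6-month) survey is randomised 1:1. Describe 300 as a minimum, not as the point at which randomisation stops.

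In Sample Size Calculation, replace the 294 with about 323 to 325, state that alpha is two-sided if that is intended, and give the power by number randomised: about 77% at 300, 80% at 325, 82% at 338 and 86% at 375.

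The cost is protocol wording and up to about 37 more youth offered the adapted digital service (half of 75). The 1:1 ratio stays, and no new cohort recruitment or surveys are needed.

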#### Randomization

In WP4, participants who meet the inclusion criteria will be randomly allocated in a 1:1 ratio using Microsoft Excel, either to receive the intervention (the adapted digital services) or to continue with usual care as part of the control group. Those assigned to the control group will not be informed that they are part of a trial or that other participants are receiving an intervention. This approach is consistent with the TwiCs design [27,33], which stages and tailors the consent process to reflect real-world clinical practice. The design ensures that individuals receiving usual care are not informed about treatments they will not be offered, thereby minimizing potential for disappointment bias.

#### Data Collection, Interventions, and Follow-Up Procedures

As part of the cohort study (WP1), the project aims to recruit up to 1500 youth aged 16 to 25 years from national minority, Indigenous, and refugee backgrounds. On the basis of currently available data, it is reasonable to estimate that the population includes between 50,000 and 65,000 youth with minority ethnic backgrounds [34-40]. Data will be collected at 3 time points (ie, at baseline, 6 months, and 18 months) using online surveys developed in collaboration with youth minority representatives and partner organizations. The surveys are available in 14 languages: Arabic, Dari, English, Farsi, French, Kven, Lule Sami, Northern Sami, Southern Sami, Norwegian, Russian, Swahili, Tigrinya, and Ukrainian. Draft versions were piloted in English, Norwegian, Arabic, and Dari with a separate sample of 1500 participants, including youth from the majority Norwegian population and those with immigrant backgrounds [41,42]. The baseline survey will serve both as a primary data collection point and as a pilot phase to evaluate and refine recruitment strategies.

The qualitative studies (WP2) aim to explore the perspectives of minority youth on digital mental health services through individual and focus group interviews depending on participants’ preferences. These interviews will examine youths’ understanding of mental health; their needs for digital services, including those related to culture, language, and gender; and their pathways to support. They will also explore experiences with service availability, approachability, acceptability, and appropriateness, including trust in services and professionals. Participant numbers will be guided by the concept of information power [43]. Interviews will be conducted, whenever possible, in participants’ preferred languages, with professional interpreters used when necessary. Interview guides have been developed in collaboration with youth representatives and project partners. All interviews will be audio recorded and transcribed verbatim.

The co-design study (WP3), which will develop recommendations for adapting digital services to better meet the needs and rights of youth from national minority, Indigenous, and refugee backgrounds, will include youth recruited through the WP1 cohort and WP2 interviews, youth representatives, co-researchers, and professionals from health and social services (eg, school nurses, psychologists, general practitioners, child welfare workers, and employment office staff). A series of 6 to 8 workshops involving youth (approximately 4‐7), professionals (approximately 4‐7), or both will be conducted. However, the number and composition of workshops may vary, as they can be conducted with a single minority group or a mix of youth from different backgrounds, depending on participant preferences and the type of input needed to inform the recommendations. Data will be collected through observations and field notes and will be enriched by findings from WP1 and WP2, youth input from a dedicated seminar, and contributions from project meetings and events. Youth will be actively involved throughout the co-design process, from planning and recruitment to facilitation, ensuring their right to be heard at the systems level, in accordance with Article 12 of the UN Convention on the Rights of the Child [44]. The resulting recommendations will be presented to service providers to support informed decisions on implementation.

The evaluation study (WP4) will assess the implementation of recommendations developed in WP3 through two complementary procedures: an RCT and a qualitative study. The RCT will use the same survey instruments as WP1, with baseline data collected at the 6-month survey (before service adaptations) and follow-up data at the 18-month survey. The qualitative study will explore youth experiences with the adapted digital services, focusing on perceived support, safety, and satisfaction. Data will be collected through individual and focus group interviews depending on participants’ preferences. They will be conducted in participants’ preferred languages with professional interpreters as needed. Participants may include both RCT participants and others exposed to the adapted services. The number of participants will be guided by the concept of information power [43], with an estimated 25 to 45 participants. Interviews will be analyzed using qualitative content analysis [45], and findings will be integrated with RCT data through mixed methods analysis, applying triangulation to assess convergence, complementarity, and discrepancies [46].

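### WP1 cohort youth who co-design the services in WP3 are not kept out of the WP4 randomisation, so some controls may already know the recommendations behind the intervention

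*Protocol article*

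**What the plan says.** **Who designs the adaptation.** The article's section on data collection, interventions and follow-up says that WP3 "will include youth recruited through the WP1 cohort and WP2 interviews", alongside youth representatives, co-researchers and professionals. Participant Recruitment describes the route: "Participants who wish to contribute further may contact the research team to express interest in taking part in qualitative interviews and co-design workshops". Study Population gives the size: "WP3 will involve a minimum of 50 youth and professionals".

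**Who is randomised.** Study Population states: "WP4 will recruit approximately 300 youth from the WP1 cohort for an RCT". Under Inclusion and Exclusion Criteria, the one additional requirement for the trial is a PHQ-9 score of 5 to 19. The stated exclusion is age: "Youth aged <16 or >25 years are excluded from participation". Having taken part in WP3 is not mentioned.

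**What controls are meant to know.** Randomization says: "Those assigned to the control group will not be informed that they are part of a trial or that other participants are receiving an intervention". It goes on to claim that the design makes sure usual-care youth are not told of treatments they will not be offered. Ethical Considerations likewise confines information about the intervention to those who are offered it.

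**The concern.** The article justifies the Trials within Cohorts design partly by what controls do not know. Study Design and Randomization credit it with limiting disappointment bias, and Study Design adds that expectations are less shaped by knowledge of the intervention. WP4 evaluates what WP3 recommended. A cohort member who helped write those recommendations and is then allocated to usual care may already know what was proposed and why.

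This matters because the primary outcome, the PHQ-9, is self-reported. A control who knows the proposals could be disappointed, which would exaggerate the difference between arms, or could seek the service out, which would dilute it. The net direction is not fixed. In the offered arm, acceptability is measured as the proportion using the service, so a co-designer's use counts directly towards it.

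Subgroup analyses by minority group are also planned, and a workshop may be held with a single group. A few co-designers could then be a noticeable share of a small subgroup. The article gives no subgroup sizes, so this cannot be quantified.

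**Working it through.** **Step 1: do the statements fit together?** WP3 draws on the WP1 cohort, and so does the trial. The stated criteria do not separate the two. The promise that controls are uninformed is made without qualification. For a co-designer allocated to control, that promise cannot be relied on.

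**Step 2: inputs.**
- Cohort 1500 and eligible share 25% (Sample Size Calculation): 0.25 × 1500 = 375 expected eligible.
- About 300 randomised 1:1 (Study Population, Randomization): 150 per arm. The chance that an eligible youth is randomised is between 300/375 = 0.8 and 1.0.
- 6 to 8 workshops with about 4 to 7 youth (Data Collection, Interventions, and Follow-Up Procedures): 6 × 4 = 24 to 8 × 7 = 56 youth.
- Assumptions: every workshop includes youth, nobody attends twice, all the youth come from the cohort, and 25% of them are eligible. None of these is stated, so a low case of 10 cohort youth is shown as well.

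**Step 3: expected co-designers among controls.** With m cohort youth in WP3, the expected number is m × 0.25 × (0.8 to 1.0) × 0.5. The chance of at least one is 1 − (1 − p)^m, with p = 0.25 × (0.8 to 1.0) × 0.5 = 0.100 to 0.125.

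| m | Expected controls | Share of 150 | Chance of at least one |
|---|---|---|---|
| 10 | 1.0 to 1.25 | 0.7% to 0.8% | 65% to 74% |
| 24 | 2.4 to 3.0 | 1.6% to 2.0% | 92% to 96% |
| 56 | 5.6 to 7.0 | 3.7% to 4.7% | 99.7% to 99.9% |

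**Step 4: harsh case for dilution.** Suppose each such control gains the full benefit. Then d becomes 0.35 × (1 − c), where c is the share of controls.
- c = 1.6%: d = 0.344.
- c = 4.7%: d = 0.334.

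After 20% dropout, 120 per arm are analysed. Two-sided power is Φ(d × √60 − 1.96):
- d = 0.35: 77.4%.
- d = 0.344: 76.0%.
- d = 0.334: 73.4%.

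The starting value is not 80% because the stated 294 does not reproduce. The two-sided formula gives 129 per arm, and 258 / 0.8 = 323 after rounding up. That is a separate matter, and nothing here depends on it.

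**Step 5: offered arm.** With 1:1 allocation the same 2.4 to 7.0 co-designers are expected there. If all of them used the service and none otherwise would have, measured uptake rises by at most 7/150 = 4.7 percentage points.

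**Step 6: effect of excluding them.** The expected eligible pool becomes 375 − 0.25 × 24 = 369, or 375 − 0.25 × 56 = 361.

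**The case against.** The strongest reply is that WP3 produces recommendations, not a service. Providers then decide what to implement. The article does not say that workshop members learn which proposals were adopted, that a trial is running, or that others were offered something. This stands. A reader might infer that some controls will know the intervention, but the documents support only that some may know the recommendations behind it.

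A reader might also count the 50 to 100 WP2 interviewees. The documents do not support that. The interviews cover needs and experiences before anything is adapted, interviewees need not be cohort members, and WP3 itself recruits from WP2, so adding them would double count.

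Nor is the randomised comparison undermined. Co-designers are randomised like everyone else and are balanced between arms in expectation. The survey items on service use, the intention-to-treat analysis and the instrumental variables analysis deal with part of any contamination. They do not deal with expectation effects on a self-reported PHQ-9, or with uptake by invested users.

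Finally, a condensed article may leave operational eligibility rules to a full protocol that is not shown. That is fair as a caution. However, the article does set out the recruitment routes, the trial criteria and an unqualified promise about controls, and as stated these do not fit together.

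**Conclusion.** The point holds in a limited form. The plan's own recruitment route can place co-designers in the control arm, contrary to its assurance that usual-care youth are not informed. On the assumptions above, about 2 to 7 of 150 controls are expected to be co-designers, and about one if only 10 cohort youth take part. At least one is likely but not certain.

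The figures rest on an unstated cohort share of WP3 and on applying the 25% eligibility rate to self-selected volunteers, who may differ from the cohort. The expected counts scale in proportion to both. The loss of power is at most about 4 percentage points even in the harsh case. The issue is therefore a concealment guarantee that the plan does not secure, not a serious threat to the average effect.

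**What to change.** Add to the trial criteria under Inclusion and Exclusion Criteria that cohort members who took part in WP3 workshops, or who serve as youth representatives or co-researchers, are not randomised in WP4. They stay in the cohort and, if exposed to the adapted services, may join the WP4 qualitative study. Apply the rule by cohort identifier before allocation, so that nobody is removed after randomisation. WP2 interviewees need not be excluded.

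The cost is about 6 to 14 of an expected 375 eligible youth, leaving about 361 to 369 before nonconsent and attrition. It is slightly higher if representatives are also in the cohort. Results reports a panel of 32, so at the same 25% rate the further expected loss is at most 0.25 × 32 = 8. The number of co-researchers is not given.

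If the sponsor cannot spare these participants, flag WP3 participation before randomisation and repeat the primary analysis without those flagged. That costs no sample, but the statements in Randomization and Ethical Considerations that controls are uninformed would then need qualifying.
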